**3. Objectives and purpose**

**3.1 Fundamentals of the study concept**

The clinical effects of iron deficiency without anaemia are difficult to assess because they overlap with many other somatic diseases or psychological complaints. Because of their gradual onset, they may go unnoticed for a long time. The perception of iron deficiency can also vary greatly depending on the personality structure of the patient. In the group of blood donors, who are highly motivated and positive compared to the average population, one could expect that complaints are noticed rather late.

A very sensitive method is required to measure the mild and unspecific symptoms of iron deficiency. The influence of inter-individual and subjective differences should be minimized as much as possible. The recording of iron deficiency-associated complaints with the help of a questionnaire alone would therefore hardly be successful. By randomized and blinded administration of iron or placebo and measurement of subjectively perceived fatigue before and after substitution of iron deficiency, these problems can be largely avoided. The good sensitivity of a numerical rating scale for quantifying the perception of fatigue is well established^5^.

Our study concept is able to avoid numerous difficulties associated with iron deficiency-associated complaints. Only the choice of intravenous iron substitution allows reliable blinding, since peroral iron preparations are always recognized by the volunteer due to their gastrointestinal side effects. Intravenous administration also solves the problem of poor drug intake, which is unavoidable due to the gastrointestinal side effects of peroral iron^19^. The intravenous infusion leads to a rapid replenishment of the iron stores. An improvement in the patient's state of health is thus much more noticeable, which significantly increases the sensitivity of the examination. Both problems are likely to play a much greater role in a similar study^22^ currently underway in Lausanne with peroral iron.

The design of our study allows the best possible blinding between verum and placebo medication. This is absolutely relevant in the difficult complex of symptoms associated with iron deficiency.

**3.2 Study objectives**

In a survey of all blood donors at our Blood Donation Centre in Bern, the extent and frequency of iron deficiency in blood donors is to be clearly recorded. The subjectively reported complaints are to be correlated with the different iron parameters and the previous donation behaviour of the test persons.

In an intervention study with intravenous iron substitution in double-blind comparison with a placebo preparation, it is to be investigated whether the subjectively felt fatigue and other general symptoms improve and thus health effects of iron deficiency can be proven without anaemia.

**3.3. Question**

**3.3.1 Survey study**

Description of the frequency and effects of iron deficiency in a large collective of blood donors.

**3.3.2 Main question of the intervention study**

Can an improvement in subjectively perceived fatigue be demonstrated by intravenous substitution of iron in blood donors without anaemia?

**3.3.3 Secondary study questions**

Do study participants subjectively feel a change in their level of fatigue after intravenous iron substitution?

Can an improvement in general and psychological well-being after intravenous iron replacement be demonstrated by means of various psychometric tests?

Can an increase in haemoglobin and an in iron stores be demonstrated after intravenous iron substitution?

How is intravenous iron replacement tolerated iby healthy blood donors?

Can an improvement in subjectively perceived fatigue be observed in the following subpopulations: Women, men, ferritin <25 μg/l, ferritin >25 μg/l, pre-existing fatigue on the numerical rating scale <4 or >4?

**3.4 Hypothesis**

Even a slight iron deficiency that has not yet led to anaemia can cause a relevant impairment of the general condition in some people. However, the complaints are so mild and unspecific that they can only be proven by comparing the condition before and after iron replacement and carefully avoiding a subjective bias.

**4. Study design**

**4.1 Overview**

The project consists of two parts, a survey study in a blood donor collective and an intervention study with intravenous iron administration in donors with ferritin levels ≤50 μg/l.

As a screening for the intervention study, all blood donors who consent to the study will be prospectively measured for about 3 months and a questionnaire on the donor history and symptoms of iron deficiency will be handed in for completion.

The main part of the project is a randomised, double-blind, placebo-controlled study with intravenous administration of iron carboxymaltose (Ferinject®) in male and female blood donors with reduced or low normal iron stores. The primary endpoint is an improvement in the level of subjectively perceived fatigue.

**4.2 Study scheme**

**First blood donation**

**Inclusion**

**Interventionstudy**

**Final visit, second blood donation**

6-8 weeks (42-56 days)

4 to 6 weeks

**Survey study blood donor cohort**

Capillary hemoglobin; blood sample: Ferritin, others (see text)

Questionnaire „Significance of iron deficiency for blood donation”

**End of study**

**Completion of questionnaires**

Blood sample: blood count (Advia 120), ferritin, Others (see text, reserved serum -70° C)

**Selection of participants (ferritin ≤50 μg/l)**

Invitation per phone to participate in the study

**Written informed consent**

**Randomisation** (with stratification)

**Completion of questionnaires**

Blood sample: blood count (Advia 120), ferritin, Others (see text, reserved serum -70° C)

**Placebo**

Intravenous infusion for 15 min

**Ferinject**

Intravenous infusion for 15 min

**4.3 Endpoints**

**4.3.1 Survey study**

The frequency and severity of iron deficiency as well as the subjective complaints associated with iron deficiency are recorded for blood donors at the Blood Donation Centre Bern. In addition, the postulated relationship between iron deficiency, clinical symptoms and previous blood donation behaviour will be investigated. To determine the iron status, several iron parameters will be measured and the diagnostic efficiency of the different parameters will be compared.

**4.3.2 Intervention study**

**Primary endpoint:**

- Difference in mean fatigue levels on a numerical rating scale of 1 to 10 between the ferinject and placebo groups four to six weeks after study drug infusion.

**Secondary endpoints:**

- Subjectively perceived change in fatigue after administration of the study drug, measured with a numerical rating scale from -10 to +10
- Improvement in general and mental well-being after intravenous iron replacement, measured by multiple psychometric tests.
- Change in haemoglobin and iron parameters after intravenous iron substitution.
- Tolerance of intravenous iron in healthy blood donors.
- Improvement of fatigue in the following subpopulations: Women, men, ferritin <25, ferritin >25, fatigue scale <4, fatigue scale >4 (see stratification criteria)

The main endpoint "fatigue" should be asked in a colloquial sense without further definition. In an earlier study, the measurement of fatigue using a numerical rating scale or a visual-analogue scale was successfully applied to women with chronic fatigue and reduced body travel^5^. With the help of this endpoint, it was possible to demonstrate a clinically relevant reduction in subjectively perceived fatigue in a statistically significant manner. Since "fatigue" is experienced by different people in very different ways, various subqualities of "fatigue" are also recorded as a secondary endpoint with the help of the Multi-dimensional fatigue symptom inventory, short form (MFSI-SF).^23^

**4.4 Procedure of the survey study**

During the recruitment phase for the intervention study (approx. 3 months), all consecutive whole blood donors of the Blood Donation Center SRC Bern are invited to participate in a study to examine their iron status. For this purpose, each donor is given an information sheet and a consent form together with the donation questionnaire. If the donor gives his or her written consent, a 2.7 ml EDTA tube and a 10 ml serum tube are also collected before the blood donation. The serum ferritin is then determined. In a random selection, the blood count and other iron parameters are determined.

The participant is asked to complete a questionnaire that includes questions about the donor's history and iron deficiency related complaints. It takes about 10 to 15 minutes to complete the questionnaire. Information on the medical history and current medication is taken from the donor documents by the study assistant.

If the participant does not participate in the intervention study and the ferritin is very low (≤50 μg/l), she/he will be informed about the result in writing. Otherwise, she/he can ask for the result by telephone or at the next donation.

**4.5 Procedure of the intervention study**

**4.5.1 Enrollment / first study visit**

Donors with a serum ferritin ≤50 μg/l qualify for the study. Potential participants are continuously selected and invited by telephone to participate in the study, taking into account the inclusion and exclusion criteria. With preliminary consent, the participant information is sent and the candidate is invited to the first study visit four to six weeks after her/his blood donation.

On the occasion of the first visit, the donor physician will provide the information. If the donor provides definite consent to participate in the study with a signed declaration of consent, the volunteer is given the questionnaire package to fill out and a blood sample is taken. From this, the blood count including erythrocyte indices (Advia 120), serum ferritin and other iron parameters are determined. Since some of the analyses are carried out later, serum is portioned and frozen at -70° C. In women of childbearing age, a urine pregnancy test is taken.

As soon as the participant has signed the consent, the nursing staff of the Clinical Investigation Unit (CIU) is informed. They randomize and stratify the patient using the study database and prepare the study medication. The finished infusion is packaged so that its color cannot be recognized. The infusion is taken to the blood donation centre and administered to the patient by the CIU nurse. In order to avoid paravenous invasions with skin discoloration, which could also affect blindness, the study drug is infused exclusively through an indwelling venous cannula (Venflon).

**4.5.2 Second study visit / study completion**

In order not to blur the effect of iron substitution, no whole blood, red cells, thrombocytes or plasma may be donated from the first blood donation at the screening until the final visit. The second, final visit takes place six to eight weeks after administration of the study drug (allowed time window 42 to 56 days). The participant is asked to complete the questionnaire package for a second time. In addition, the study coordinator will ask about any side effects on the study medication. Blood is then sampled and the blood count and various iron parameters are determined again. The material is frozen at -70° C. The study is now completed for the participant. If she or he wishes, a regular blood donation may be made at the end of the study.

Following this visit, the participant is informed in writing whether he or she has received the iron supplement or the placebo. In addition, the laboratory results of the first visit and the ferritin value of the second visit will be sent to the volunteer.

**4.5.3 Study medication**

Iron carboxymaltose (Ferinject®)

Iron carboxymaltose has been authorised in Switzerland by Swissmedic since 2008 for the treatment of iron deficiency. The drug is provided free of charge by the company Vifor Pharma Ltd. It is administered in a 0.9% NaCl carrier solution as an intravenous infusion. The dose was determined as follows:

**► 800mg Iron carboxymaltose**

→ 16ml Ferinject in 200ml 0.9% NaCl as short infusion over 15 min intravenously

Placebo

The placebo is an unstained 0.9% NaCl solution. A placebo preparation identical in colour to the verum is not available. In order to ensure blindness, the study drug is administered by an external nurse with an eye-protected infusion bag and infusion set.

**4.6 Randomization and Blinding in the Intervention Study**

The participants are randomized to the verum or placebo group in a 1:1 double-blind ratio. Stratification is performed according to the ferritin value at screening (≤25 μg/l or >25 μg/l), gender and the degree of pre-existing fatigue (<4 points versus ≥4 points on the numerical rating scale). Randomisation and stratification is carried out by the nurses of the Clinical Investigation Unit using the computer of the study database.

Since the placebo and the verum preparation differ in colour, the preparation and administration of the infusion must be carried out by an external person who is not otherwise involved in the care of the subjects. This task is performed by nurses from the Clinical Investigation Unit (CIU) of the Inselspital. The nurses of the CIU randomize the participants on the computer, bring the prepared infusion to the blood donation center and administer it. With the help of black colored infusion tubes and by covering the infusion bag with cloths, it is ensured that neither the test person nor the staff of the blood donation center can find out the study arm. Iron carboxymaltose is associated with slightly more frequent side effects compared to placebo^24^. Especially gastrointestinal complaints and general symptoms have been described. However, the extent of these side effects is so small that they will not have any relevant influence on blinding and thus statistical significance.

**4.7 Premature study termination**

The participant can withdraw from the study at any time without giving a reason and withdraw his/her declaration of consent. In this case, no further data will be collected and all blood samples will be destroyed. However, data already collected will be included in the statistical analysis of the study. If the study drug has already been administered, a final medical examination will be performed at the request of the participant.

**4.8 Care of the participants**

In the survey study, the blood donor information and data collection is supported by the nursing staff of the blood donation service. The intervention study is supervised by the study assistant specially employed for the study. She works independently of the blood donor service. She is responsible for the recruitment and information of the volunteers, the care of the participants in the blood donation centre and the completion of the questionnaires. Before the study drug is administered, the donor physician checks and verifies the declaration of consent and answers any additional questions the participant may have about the study.

**5. Selection of study participants**

**5.1 Survey study**

Consecutive blood donors at the Blood Donation Centre Berne ([name]) of the Blood Donation Service of the SRC Berne Ltd. are invited to participate in a survey study on iron deficiency on the occasion of their donation. The donor must agree to an additional blood sample and to answer a questionnaire.

**5.1.1 Inclusion criteria**

- Signed consent form

- Whole blood donors suitable for donation

**5.1.2 Exclusion criteria**

- Active disease or medication associated with fatigue

- Limited ability to understand the consent form

- Limited ability to complete the questionnaire

- Initial donor

**5.2 Intervention study**

All participants in the survey study with a serum ferritin ≤50.0 μg/l who meet the inclusion criteria and have no exclusion criteria will be invited to participate in the intervention study by telephone by the study coordinator.

**5.2.1 Inclusion criteria**

- Participation in the overview study

- Donation suitability

- At least one previous blood donation

- Signed declaration of consent

- Serum ferritin ≤50.0 μg/l

**5.2.2 Exclusion criteria**

- Anemia: Hemoglobin <121 g/l (♀) or <135 g/l (♂)

- Previous intolerance reaction to intravenous iron

- Undergone anaphylactic reactions

- Active systemic infections of any kind

- Known congenital or acquired iron overload (hemochromatosis)

- indications of acute or chronic bleeding, especially gastrointestinal

- Active disease or medication that would explain increased fatigue (at the discretion of the study director/donor physician)

- Active disease or medication that makes intravenous iron replacement not advisable (at the discretion of the study director/donor physician)

- Body weight <50 kg and >85 kg (♀) / >100 kg (♂)

- Age <18 years or >70 years

- Pregnancy and breastfeeding

- Limited ability to complete the questionnaires

- Limited ability to understand the consent form

**6. Measurements**

**6.1 Survey study**

**6.1.1. Questionnaire**

Each participant is asked to complete a questionnaire. This questionnaire consists of 14 questions and evaluates the following topics:

- Previous donor behaviour (2 questions)

- Pre-existing anemia (2 questions)

- Subjectively perceived fatigue (numerical rating scale from 1 - 10)

- Physical performance (numerical rating scale from 1 - 10)

- Concentration ability (numerical rating scale from 1 - 10)

- Loss of drive (numerical rating scale from 1 - 10)

- Depressive mood (Two numerical rating scales from 1 - 10)

- Hair Loss

- Changes in fingernails

- Fatigue caused by blood donation (2 questions)

**6.1.2. Laboratory analyses**

During routine donation preparations, capillary haemoglobin level is determined. A 2.7 ml EDTA tube and a 10 ml serum tube are collected from each participant. The serum ferritin level is then determined in each participant. In a random selection of all participants (one fifth of participating persons), a complete blood count including erythrocyte indices, CRP, soluble transferrin receptor, transferrin saturation, zinc protoporphyrin and serum hepcidin is also determined. Since some of the analyses are performed "en bloc" at a later date, the material is portioned and frozen at -70° C.

**6.2 Intervention study**

**6.2.1. Questionnaires**

The psychometric assessment is carried out with standardised questionnaires validated in German by participants self-report in terms of the following dimensions:

1) Tiredness (fatigue)

2) Health-related quality of life

3) Psychological distress / mood

The questionnaires are handed out to the participants as a booklet. The participant answers the questions independently, and the study coordinator is available in case of any uncertainties. The answering of the questions takes place in the blood donation centre and takes about 30 minutes.

The numerical rating scale from 1 to 10 for the symptom fatigue (main endpoint) was tested in a preliminary trial with 79 healthy blood donors. The median fatigue level was 3, with only 7 of 79 of participants indicating the lowest possible value of 1. Nine of 79 participants quantified their level of fatigue as 2, 29 of 79 as 3, and 24 of 79 indicated a value of 5 or higher. Thus, the test is well suited to measure fatigue and allows almost all subjects to indicate also low levels of fatigue.

At the second visit, an additional numerical rating scale with a range from -10 to +10 is used to determine whether the participant’s fatigue has changed subjectively (secondary endpoint).

Applied tests:

- Perception of fatigue with a numerical rating scale from 1 to 10^5^

- Numerical rating scale from -10 to +10 for the subjectively perceived change in

fatigue (at second study visit only)

- Multi-dimensional fatigue symptom inventory, short form^23^ (MFSI-SF): 30 items

- EUROQol for quality of life^25^ (EQ): 6 items

- Symptom checklist SCL-27^26^ (SCL-27): 27 items

- Jenkins sleep questionnaire^27^ (JSQ): 4 items

**6.2.2. Laboratory analyses**

At both the first and second visit, 10 ml serum and 2.7 ml EDTA blood are collected. The blood count including erythrocyte indices (Advia 120), CRP, serum ferritin, transferrin saturation, soluble transferrin receptor, zinc protoporphyrin and serum hepcidin are determined. Since some of the analyses are performed "en bloc" at a later date, the material is portioned and frozen at -70° C. In women of childbearing age, a urine pregnancy test is carried out before the participant is included in the study.

**7. Safety**

**7.1 Safety profile of the trial drug**

Iron carboxymaltose (Ferinject®) has been approved in Switzerland since 2008. The preparation is intended to be administered in medical practices without special safety equipment. Iron carboxymaltose (Ferinject®) has a very favourable side-effect profile^28^. Most common are reactions at the injection site. Mild headaches, gastrointestinal complaints and skin rashes are also observed. Anaphylactic reactions, as feared with earlier intravenous iron preparations, are a great rarity with Ferinject®. The Blood Donation Centre in Berne would be ideally prepared to treat such complications. The dose was chosen so that no volunteer would suffer from iron overload.

**7.2 Definitions**

**(See also Appendix B, page 13)**

**7.2.1. adverse event (AE)**

For the purposes of this protocol, an adverse event (adverse event = AE) is any occurrence or worsening of a symptom, pathological finding or medical condition during or after administration of the study drug, regardless of whether a relationship with the study drug is suspected. Side effects are evaluated by means of open questions. If available, more detailed and specific questions follow. A physical examination, special laboratory tests or other tests for detection are not routinely performed and are only ordered if the severity or nature of the condition medically requires it.

**7.2.2 Serious adverse event (SAE)**

A serious adverse event (SAE) is any adverse reaction that

- results in death

- is life-threatening

- requires hospitalization

- results in continuing disabilities

- leads to congenital anomalies / birth defects in a child

- is otherwise medically significant (in the opinion of the examiner)

**7.2.3 Adverse drug reaction (ADR)**

An adverse drug reaction (ADR) is any harmful or undesirable reaction to the study drug, if a relationship with the study drug must be suspected. It can be a known adverse reaction or one that has never been described before.

**7.2.4 Suspected unexpected serious adverse reactions (SUSAR)**

A suspected unexpected serious adverse reaction (SUSAR) is any adverse reaction that has already been described but was more serious than described in the medication information.

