**7.3 Documentation and evaluation of side effects**

**(See also Appendix B, pages 14 to 16)**

The severity of side effects is classified according to the NCI v.3.0 criteria. All side effects and all therapies administered for their treatment are recorded in the patient documentation and in the eCRF. If side effects are still present at the second study visit, they are tracked until they disappear (by telephone if medically justifiable). SAEs are also listed on a special SAE form. Whether there is a correlation with the study medication is assessed as described in Appendix B, point 4.3.

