**7.4 Notification of adverse events and annual safety report**

**(See also Appendix B, pages 17 to 35)**

The Principal Investigator as investigator/sponsor of the study ensures that all SAEs and SUSARs are reported to him/her by the study team, usually on the same day. He ensures that an authorised and competent deputy is always available in case of absence.

Life-threatening and fatal SAEs are immediately reported to the Cantonal Ethics Committee (CEC). The remaining SAEs are summarised in an annual safety report for the attention of the CEC Berne. Serious Adverse Drug Reactions (SARs) and SUSARs are reported to the Cantonal Ethics Committee and Swissmedic in accordance with official guidelines. The exact procedure is described in Appendix B, point 4.5.3.

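### The SUSAR definition omits serious reactions never described before, and the SAE definition says reaction where the rest of section 7 needs event

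*Protocol*

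**What the plan says.** Section 7.2 of the protocol sets out four safety terms and points to Appendix B for more.

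- **AE (7.2.1):** any new or worsening symptom, finding or condition during or after study drug, "regardless of whether a relationship with the study drug is suspected".
- **SAE (7.2.2):** "A serious adverse event (SAE) is any adverse reaction that" meets one of six seriousness criteria.
- **ADR (7.2.3):** a harmful or undesirable response for which a link to the study drug must be suspected. "It can be a known adverse reaction or one that has never been described before".
- **SUSAR (7.2.4):** "any adverse reaction that has already been described but was more serious than described in the medication information".

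Sections 7.3 and 7.4 attach duties to these terms. Under 7.3, SAEs go on a dedicated form, and "Whether there is a correlation with the study medication is assessed as described in Appendix B, point 4.3". Under 7.4, the study team notifies the investigator/sponsor of SAEs and SUSARs, usually the same day. Fatal and life-threatening SAEs go at once to the ethics committee, and the other SAEs go into the annual safety report. In addition, "Serious Adverse Drug Reactions (SARs) and SUSARs are reported to the Cantonal Ethics Committee and Swissmedic in accordance with official guidelines". At the final visit (4.5.2), "the study coordinator will ask about any side effects on the study medication".

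**The concern.** Two of the four definitions do not fit their neighbours. The SUSAR definition ties unexpectedness to prior description, so the plainest unexpected case, a serious reaction absent from the medication information, does not qualify. The SAE definition uses the word that 7.2.3 reserves for a suspected link to the drug, so on its face it makes causality a condition of being an SAE.

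Staff sort events by these definitions, and the SAE form and the notification steps in 7.3 and 7.4 are triggered by the defined terms. Proof of safety in blood donors is a stated aim (section 1), and tolerance is a secondary endpoint (4.3.2). The wording therefore matters for how serious events are classified and passed on.

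**Working it through.** No arithmetic applies, and the plan gives no figure to reproduce. The check is to sort test cases through the text of 7.2 to 7.4.

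| Category | Case 1: serious, suspected, never described before | Case 2: serious, judged unrelated |
|---|---|---|
| AE (7.2.1) | Yes | Yes |
| SAE (7.2.2) | Yes | No, if reaction is read literally |
| ADR (7.2.3) | Yes, expressly included | No |
| SAR (7.4) | Yes | No |
| SUSAR (7.2.4) | **No** | No, and rightly so |

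**Case 1.** The only category lost is SUSAR. As an SAE, the reaction still goes on the SAE form (7.3) and to the investigator/sponsor, usually the same day (7.4). If fatal or life-threatening, it still goes at once to the ethics committee. As a SAR, it still goes to the ethics committee and Swissmedic. Whether SARs and SUSARs are handled differently from there on is left to Appendix B, point 4.5.3, which is not at hand. The inconsistency is between 7.2.3, which foresees a reaction not described before, and 7.2.4, which leaves it out. Section 7.2.4 also does not refer back to the seriousness criteria of 7.2.2, so its comparison with the medication information could be taken as one of severity only.

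**Case 2.** The event remains an AE. If it is not an SAE, four steps are not triggered:

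1. the SAE form (7.3);
2. the same-day notification (7.4);
3. the immediate ethics committee report, if fatal or life-threatening (7.4);
4. the annual safety report (7.4).

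The surrounding text shows that the literal reading conflicts with the rest of section 7. Section 7.2.1 makes the AE independent of causality. Section 7.3 mentions the SAE form and then treats the relationship to study drug as something still to be assessed. Section 7.4 lists SARs separately from SAEs, a distinction with little content if every SAE were already a drug reaction.

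**Final-visit question.** Section 4.5.2 asks about side effects, and 7.3 records side effects. Neither uses the AE term. However, 7.2.1 itself uses side effects, together with open questions, inside its causality-free definition, so the word may simply be a synonym. This supports a wording alignment and nothing stronger.

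**The case against.** The strongest reply is that the protocol uses event, reaction and side effect loosely throughout. Section 10.2 calls SAEs, SARs and SUSARs together serious adverse reactions. The title of 7.4 says reactions in the table of contents and events in the text. On that view the SAE wording is a slip, and the structure of 7.3 and 7.4 shows what was meant. Appendix B, cited in 7.2, 7.3, 7.4 and 10.2, may also carry complete definitions.

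Much of this stands. The literal reading of 7.2.2 may not be the intended one, and the effect on actual reporting cannot be settled from the protocol alone. The reply does not rescue the wording. Section 7.2 cites Appendix B only as a further reference and does not say that it prevails. If the appendix is right, the protocol disagrees with it; if it is not, the gap is real. Nor does loose usage explain 7.2.4, where the restriction to described reactions is explicit.

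Three stronger readings are tempting, and the documents support none of them.

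- A reader might infer that these cases fall outside the trial's safety categories altogether. They do not, as the sorting of both cases shows.
- A reader might infer that the tolerability comparison is filtered by attribution. The use of side effects in 7.2.1 speaks against that. Participants and donation-centre staff are blinded (4.6), and the protocol states no between-arm test of tolerability; 2.4 says only that the side-effect spectrum is to be described.
- A reader might note that zero events in 200 treated donors leaves an upper 95% bound of about 3/200 = 1.5%, and argue that one misclassified event would change the safety conclusion. That bound describes precision when nothing is observed and says nothing about definitions. A reaction without the SUSAR label is still recorded, so it is not lost from any count.

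**Conclusion.** The point holds as a defect in two definitions. Section 7.2.4 leaves out the suspected serious reaction never described before, which costs that reaction its SUSAR label but not its reporting to the ethics committee and Swissmedic. Section 7.2.2 conflicts with 7.2.1, 7.3 and 7.4; on a literal reading, a serious event judged unrelated keeps AE status but misses the four SAE steps.

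The size is modest. The primary endpoint and its analysis are not touched, and no number in the plan changes. The conclusion rests on the protocol text alone, with Appendix B unseen, and for 7.2.2 on taking the word reaction in the sense of 7.2.3. It is worth correcting because these terms decide which form and which notification route a serious event takes.

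**What to change.** Make two wording changes:

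- **7.2.4:** define a SUSAR as a suspected serious adverse reaction whose nature or severity is not consistent with the medication information.
- **7.2.2:** define an SAE as any adverse event, whether or not related to the study drug, that meets one of the listed criteria.

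Then reconcile both with 7.2.1, 7.2.3, 7.3, 7.4 and Appendix B. As a minor alignment, use the term adverse events in the final-visit question (4.5.2) and in 7.3, leaving causality to the separate assessment that 7.3 already provides for.

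The cost is a short text amendment and a matching change to the final-visit question. A few more events may be entered. Design, sample size and analysis are unaffected.
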